#### Dose limiting toxicology

The DLT assessment period is 12 weeks from the start of treatment.

Any of the following events occurring after the first dose of tolinapant will constitute a DLT if, in the opinion of the investigator, the event is defined as definitely or probably related to tolinapant:

Grade 4 neutropenia ≥ 7 days duration.Grade 3 or 4 febrile neutropenia (neutrophils < 1000/mm3 with a single temperature of > 38.3 °C or a sustained temperature of ≥ 38 °C for more than one hour AND/OR life-threatening consequences with urgent intervention indicated).Grade 3 or 4 neutropenia associated with a separate event of bacteriologically proven sepsis happening at the same time.Grade 3 or 4 thrombocytopenia.Death.

Any other grade 3 or 4 adverse event will constitute a DLT if, in the opinion of the investigator, the event is defined as definitely or probably related to tolinapant.

In all cases of a suspected DLT, clinical judgement will be the final arbiter as to whether the event should be categorised as such.

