#### Sample size and recruitment

The actual number of patients required and the duration of the trial will depend on any toxicities observed and dose escalation decisions. As a result of the stopping rules (see additional file 1), all simulated toxicity scenarios, using the stats package R, averaged 24–29 participants, while a maximum of 42 patients was deemed suffient to estimate the MTD and be able to recruit additional patients to ensure 18 are treated at the recommended phase II dose. In order to ensure adequate recruitment, the trial will include patients with a wide range of cervical cancer stages; including those with radiologically active pelvic nodes. In addition the chosen trial sites for CRAIN are geographically widespread throughout the UK and press releases are timed alongside key site openings to enhance recruitment.

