#### Dose escalation and determination of MTD

The trial will be a single arm, open-label, multi-centre trial that will use the two-stage time-to event continual reassessment method (TiTE-CRM) to find the optimal dose of tolinapant in combination with CRT. This method assigns weights to the amount of time a patient spends in the study without experiencing a DLT and allows for dose decisions to be made without having to wait for full information from each participant enrolled. This allows for a potentially shorter trial duration without sacrificing valuable data. Simulations (see additional file 1) were run to see how this design perfomed under a range of scenarios for the true toxicity levels of the doses and to compare with a standard 3 + 3 cohort design. The optimal dose will be defined as the dose where the proportion of patients experiencing a DLT is closest to the target toxicity rate. DLTs for existing treatment is thought to be in the range 5 to 15%. The target toxicity rate was therefore chosen as 25% as an acceptable rate above this.

Dose levels for tolinapant which will be assessed in the TiTE-CRM are: Level 1: 60 mg; Level 2: 90 mg (starting level); Level 3: 120 mg; Level 4: 150 mg; Level 5: 180 mg. No dose skipping is allowed (i.e., it is only possible to escalate to an adjacent dose). These doses were thought to cover a range of outcomes from a low number of DLTs to those plausibly at, or potentially beyond, the target toxicity rate. The two-stage design allows more control of the dose escalations in the early stages of the study when no DLTs have occurred. The TiTE-CRM model together with emerging safety data will guide escalation decisions but all decisions will be made by the SRC.A maximum of 42 patients will be recruited and treated according to the dose defined by the TiTE-CRM. The first patient recruited will be assigned 90 mg as this will allow for a dose reduction to 60 mg for future patients if the first patients experience excess toxicity. The TiTE-CRM will identify the MTD based on the assessment of dose limiting toxicities (DLTs), this will be used to aid the SRC when determining the recommended phase II dose.

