The TiTE-CRM design utilises a one parameter logistic model and linear weights. Meaning that information accrued through the DLT assessment period (12 weeks from the start of treatment) is given weight equal to the proportion of the assessment period that has passed. Any patient experiencing a DLT will be included in the analysis as a full patient equivalent, regardless of the timing of the event. Any patient who discontinues treatment early, for any reason not attributable to a DLT, will be included in the analysis as a patient without a DLT. The Safety Review Committee (SRC) will decide whether an extra patient should be recruited to the current dose based on the amount of treatment they had received.

The treatment schedule is planned to last 7 weeks, with an additional 5 weeks follow up for DLTs. Linear weighting will be used in the TiTE-CRM. For example:

At trial week 12 (i.e. completion of treatment and 5 weeks of follow-up): in the absence of a DLT this would account for a full patient tolerable outcome.At trial week 6: in the absence of a DLT this would account for 0.5 equivalent of a tolerable outcome.

The trial will stop for success if 15 consecutive patients are treated at the current recommendation for the MTD, whilst also ensuring a total of at least 18 patients have been treated at the recommended phase II dose. The trial will stop for safety if there is sufficient evidence to suggest that dose level 1 (60 mg) is too toxic i.e. a posterior probability of DLT of 35% or higher is found reflecting a 10% increase over the expected toxicity rate based on published experience [3]. For more information on the TiTE-CRM design and the stopping rules for the study please see additional file 1.A SRC will be responsible for confirming trial dose escalations within the trial, informed by the dose-toxicity model and safety data. The SRC will decide if patients should be replaced based on the amount of treatment received.

If a fifteenth consecutive participant is treated at a given dose and 18 patients overall have been treated at this dose, no more participants will be recruited. All participants should then be followed up until a DLT or 12 weeks, the model and the MTDare then updated with this information, and this is used to inform the SRC’s decision on the final recommended phase II dose.

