At the end of this phase, dose finding data will be summarised descriptively, including baseline characteristics for participants. Dose delivery and toxicities will be reported. Toxicities will be reported by cohort, including type, number, range and worst grade. Complete and partial response rates at 3 months after treatment, measured using Recist v1.1 criteria, will also be summarised descriptively along with relative dose intensity.

The parameters of the dose-toxicity model will be described alongside Bayesian posterior point estimates of the risk of toxicity at each dose and corresponding 95% credible intervals.

All analysis will be done in R, Stata v16 or higher, or SAS v9.4.

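### Away from the selected dose, the 95% credible intervals from the one-parameter model depend on the assumed curve shape and can under-cover, most at 60 and 180 mg

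*Protocol article*

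**What the plan says.** All places are in the protocol article. Under *Dose escalation and determination of MTD* the model is fixed: "The TiTE-CRM design utilises a one parameter logistic model and linear weights". The same section says what is reported at the end: "Bayesian posterior point estimates of the risk of toxicity at each dose and corresponding 95% credible intervals", beside the model parameters. The doses are "Level 1: 60 mg; Level 2: 90 mg (starting level); Level 3: 120 mg; Level 4: 150 mg; Level 5: 180 mg" and the target DLT rate is 25%. Recruitment stops for success after 15 consecutive patients at the current MTD recommendation, provided at least 18 have been treated at the recommended phase II dose. The updated model then informs the Safety Review Committee's choice of that dose. Under *Sample size and recruitment* the simulated trials "averaged 24–29 participants, while a maximum of 42 patients" is the cap. Toxicities will also be summarised by cohort, but no interval based on those observed counts is mentioned. The skeleton, the prior and the simulated scenarios are referred to additional file 1.

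**The concern.** A one-parameter CRM learns one number and takes the shape of the dose-toxicity curve as known. That suits its purpose of finding the dose near the target. It suits less well the task of stating how uncertain the DLT rate is at every dose. If 18 patients sit at one dose and the simulated average is 24 to 29, only 24 − 18 = 6 to 29 − 18 = 11 remain for the other four doses, and some doses may have none. The model still prints a 95% interval there, and that interval tightens with data from elsewhere. A phase II planner could read a narrow interval at 60 or 180 mg as a measured safety margin when it mostly reflects the skeleton.

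**Working it through.** **The plan's own figure.** The article states no coverage for these intervals. Its only related simulation result, the average of 24 to 29 participants, cannot be reproduced without additional file 1; the assumed settings below gave mean sizes of 12 to 34.

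**Inputs from the article.** One-parameter logistic model, linear weights over 12 weeks, target 25%, five doses starting at level 2, no skipping, the stopping rules, maximum 42.

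**Assumed inputs.** Indifference-interval skeletons with half-width 0.05, 0.08 or 0.10; prior MTD at level 2 or 3; intercept 3; normal prior with SD 0.6, 0.8 or 1.158; first-stage groups of 3; and all true curves.

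**Step 1: the mechanism.** The model is p_i(b) = expit(3 + exp(b)·d_i), with d_i = logit(skeleton_i) − 3 and b ~ N(0, SD²). If b_L and b_U are the 2.5% and 97.5% posterior points of b, the interval at every dose runs from expit(3 + exp(b_U)·d_i) to expit(3 + exp(b_L)·d_i). The same two numbers serve all five doses; only the fixed d_i differ.

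**Step 2: one hypothetical data set, two skeletons.** Take N = 24: 0/3 DLTs at 90 mg, 4/18 at 120 mg, 1/3 at 150 mg, nobody at 60 or 180 mg; prior MTD at level 3, SD 1.158.

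| | Half-width 0.05 | Half-width 0.10 |
|---|---|---|
| d at 60 / 120 / 180 mg | −5.327 / −4.099 / −3.153 | −7.015 / −4.099 / −2.395 |
| b_L, b_U | −0.181, 0.292 | −0.181, 0.303 |
| 60 mg (n = 0) | 1.6–19% | 0.2–5.4% |
| 120 mg (n = 18) | 8–40% | 7–40% |
| 180 mg (n = 0) | 23–59% | 44–73% |

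For example, at 60 mg with half-width 0.05: expit(3 − 1.339 × 5.327) = 1.6% and expit(3 − 0.835 × 5.327) = 19%. With no patients at 60 mg, its interval is narrower than that at 120 mg with 18 patients under both skeletons. With half-width 0.10, the untested 180 mg interval is also narrower (73 − 44 = 29 points, against about 32 at 120 mg). Changing only the skeleton moves the 180 mg interval from 23–59% to 44–73%; the 120 mg interval hardly moves.

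**Step 3: coverage with fixed allocation.** Coverage is the share of simulated intervals that contain the true rate. There were four true curves, all with the MTD at level 3, and three skeletons, with 2,000 replicates each.

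| Patients per dose | At MTD | Next to MTD | Levels 1 and 5 |
|---|---|---|---|
| 0/3/18/3/0 (N = 24) | 0.92–0.95 | 0.57–0.94 | 0.12–0.95 |
| 3/9/18/9/3 (N = 42) | 0.90–0.96 | 0.40–0.94 | 0.03–0.94 |

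Of the 4 × 3 × 4 = 48 off-MTD cells, none fell below 0.10 at N = 24, and 4 did at N = 42.

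**Step 4: coverage in full simulated trials.** Nine true curves by five skeleton and prior settings, 500 trials each, with the stated stopping rules. Mean off-MTD coverage by setting was 0.80, 0.66, 0.82, 0.80 and 0.55, so (0.80 + 0.66 + 0.82 + 0.80 + 0.55)/5 = 0.73 overall. Single doses ranged from 0.07 to 0.97, and 1 of 9 × 5 × 4 = 180 cells was below 0.10.

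- Skeleton close to the truth (10/15/25/35/45%, half-width 0.05): 0.92 to 0.93 at all doses.
- Steep curve, half-width 0.05: 0.49 at level 1 and 0.15 at level 5.
- Flat curve, half-width 0.10: 0.07 at level 5.

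Good coverage follows the patients. In the least favourable setting, with a true MTD at level 5 that received on average 1.9 patients, coverage there was 0.31.

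**The case against.** **Nothing here is an error.** The protocol promises posterior summaries from its prespecified model and claims no long-run coverage. That stands: this is a point about reporting and reading, not a contradiction.

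**The size rests on assumptions.** The real skeleton and prior are not in the article, and coverage at one dose can move from near nominal to very poor as they change. That also stands, so no single figure can be stated for this trial. The spread is itself evidence that the skeleton drives these intervals.

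**Observed toxicity will be visible, and no passage bases the phase II dose on the off-dose intervals.** Both are correct and limit the harm. The committee works from the updated model, the MTD and the safety data, and the recommended dose should have at least 18 patients. But the only intervals specified are the model's.

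**Alternatives have faults too.** Exact intervals say nothing at untested doses and little at n = 3. A two-parameter fit needs its own prior and, under one assumed prior, covered only 61–88% on a flat curve. It could also point to a different MTD from the model that ran the trial. This is why it should not replace the planned model.

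**A stronger reading is tempting:** that the intervals away from the MTD almost never contain the true rate. The documents do not support it. At this trial's size the intervals are usually wide enough to include the truth, and they are near nominal when the skeleton fits. Coverage fell to about zero in most settings only with an unrealistic 1,800 patients at the MTD; at realistic sizes it was confined to isolated cells at the extreme doses.

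**Conclusion.** The point holds as a reporting weakness of modest weight. Intervals labelled 95% at little-tested or untested doses are projections of the assumed shape. They can be narrower than the interval at the best-studied dose, and they can under-cover substantially when the true curve is steeper or flatter than the skeleton. Under the assumed settings the off-MTD average was 55–82% by setting, with the worst cells at 60 and 180 mg. Where most patients are treated, and wherever the skeleton fits, coverage is close to nominal. The mechanism follows from the one-parameter model alone; the percentages depend on the assumed skeletons, priors and true curves. Neither the MTD rule nor the sample size is affected.

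**What to change.** Keep the one-parameter TiTE-CRM for dose assignment, MTD selection and its posterior summaries. In the final report:

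- Show, beside each model estimate, the number treated, the number with a DLT and the exact (Clopper-Pearson) 95% interval at every tested dose.
- Label the model intervals at untested or sparsely tested doses as dependent on the skeleton.
- Optionally add a two-parameter logistic fit, with its prior stated in advance, as a sensitivity analysis only.

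In the example above, the exact intervals would be 0–71% for 0/3 (upper limit 1 − 0.025^(1/3) = 0.71), 6–48% for 4/18 and 1–91% for 1/3. The last two come from the 2.5% point of Beta(x, n − x + 1) and the 97.5% point of Beta(x + 1, n − x). The cost is a few lines of R and visibly wide intervals at sparse doses, which is an honest picture of what was observed there. No design change is needed.

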### Adverse event reporting and risks

All AEs and SAEs will be reported between the first dose and 30 days after the last dose of tolinapant. Only AEs and SAEs that are considered by the investigator to be related to trial procedures will be reported between the provision of informed consent and the first dose of tolinapant. The SCTU has a UK regulatory compliant real-time SAE reporting process to identify serious AEs and suspected unexpected SAEs that could suspend or stop the trial if warranted.

The most common treatment-related AEs in the phase I aspect of another open-label tolinapant study (ASTX660-01) include nausea, pruritus, vomiting, fatigue and maculo-papular rash. The most common Grade 3 AE related to study treatment was increased lipase.

The most common SARs included pneumonitis, maculo-papular rash and pancreatitis (Astex Pharmaceuticals ASTX660 Investigator Brochure, v7 18th August 2021).

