#### Treatment and follow-up visits

Treatment will consist of standard of care CRT with 45 Gy external beam radiotherapy administered in 25 daily fractions over 5 weeks with once weekly cisplatin 40 mg/m2. RT visit assessments include ECOG performance status, routine bloods, pregnancy tests for WOCBP (weeks 3 & 5) and adverse event assessment (weeks 1, 3 & 5). Six PK samples will be taken across day 4 and day 5 of week 1.

Tolinapant will be administered in fixed dose capsules of 30 mg or 90 mg taken orally daily for seven consecutive days as an outpatient (followed by seven consecutive days off) prior to radiotherapy on alternate weeks (weeks 1, 3, 5) during chemoradiation. As tolinapant will be administered as an outpatient, and in order to assess IMP administration adherence, patient diaries will be reviewed and capsule returns monitored. Tolinapant can be taken with or without food, with the exception of PK days. On days with PK sampling, patients should refrain from eating (including soup) or drinking milk or juice for at least 2 h prior to ingesting study drug(s) and 2 h after ingesting study drug (4 h fasting window).

This is followed by standard of care brachytherapy. Assessments during brachytherapy visits will include physical exams, ECOG performance status, routine bloods (week 6 only) and adverse event assment (week 7 only).

Patients will then attend a follow-up visit at weeks 12 and 18, involving physical exams (including vaginal adhesions at week 18), ECOG performance status, adverse event assessment, MRI (week 18 only) and Disease Assessment Questions (week 18 only).

The Schedule of Events (Table 2) details the trial treatment schedule.

**Table 2 Tab2:** Schedule of observations and procedures

	Screening Phase	Treatment Phase							Follow up Phase	
		External Beam RT Treatment Week 1	External Beam RT Treatment Week 2	External Beam RT Treatment Week 3	External Beam RT Treatment Week 4	External Beam RT Treatment Week 5	Brachytherapy Week 1	Brachytherapy Week 2	Follow up visit 1	Follow up visit 2
Trial Week^1^	-2-0 weeks	1	2	3	4	5	6	7	12 (± 1 week)	18 (± 1 week)
Informed consent^2^	x									
Inclusion / exclusion criteria	x									
Medical history	x									
Physical exam	x						x	x	x	X^3^
ECOG performance status	x	x	x	x	x	x	x	x	x	x
Electrocardiogram	x									
Echocardigram	x									
Serum biochemistry^4^	x	x	x	x	x	x	x			
Haematology^5^	x	x	x	x	x	x	x			
Serology – HBV and HCV	x									
Pregnancy test for WOCBP^6^	x			x		x				

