Translational tissue samples^7^	x						x			
Translational blood samples	x	x	x	x	x	x	x	x	x	
Translational urine samples	x	x		x		x	x		x	x
Diagnostic imaging assessment (MRI)	X^8^					x				X
CT scan to assess for metastases^9^	x									
Disease Assessment Questions^10^	x					x				x
Adverse event assessment	x	x		x		x		x	x	x
Concomitant medication record	x								x	x
Tolinapant^11^		x		x		x				
PK sampling^12^		xxxxxx								
External beam radiotherapy (standard 5 week course)^13^		x	x	x	x	x				
Cisplatin (40 mg/m^2^)		x	x	x	x	x				
Brachytherapy^14^							x	x		

^1^Treatment weeks of CRT and tolinapant should always be scheduled to start on a Monday, cisplatin can be given on any day throughout the week

^2^Consent may be taken up to 14 days prior to Treatment day 1, week 1 and must be completed before any screening procedures take place

^3^Vaginal adhesions should be assessed as part of the physical exam at the follow up 2 visit to inform the disease assessment

^4^Serum biochemistry including renal (urea, sodium, potassium, creatinine), liver (AST and ALT, ALP and bilirubin), bone (including serum albumin and calcium), thyroid profiles (including T4, T3, TSH) and lipids, lipase and amylase. Bloods required on the day of treatment can be taken up to one working day in advance

^5^ Full blood count (FBC) to include haemoglobin, white blood cell count, absolute neutrophil, lymphocytes and platelets counts. Bloods required on the day of treatment can be taken up to one working day in advance

^6^Must be serum test at screening. Urine/serum test at week 3 and week 5

^7^ Archival FFPE block to have been collected within 3 months prior to day 1 and should be sent as soon as possible after consent. New tissue biopsy to be collected at week 1 Brachytherapy

^8^Screening scan not required if done within 8 weeks prior to day 1

^9^Baseline imaging assessing for metastases can be done via CT alone or combined PET-CT, and does not need to be repeated if done within 8 weeks prior to day 1

^10^Assessment of fecal urgency (RT-ARD Score) at screening, Radiotherapy week 5 and follow up 2. Assessment of vaginal dilator use at follow up 2 only

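### Adverse event reporting closes on day 65 of a full course, but the DLT window that feeds the TiTE-CRM runs to day 84; the two rules need to be reconciled

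*Protocol article*

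**What the plan says.** Four parts of the protocol article bear on how long toxicity is captured.

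- *Adverse event reporting and risks*: "All AEs and SAEs will be reported between the first dose and 30 days after the last dose of tolinapant". No exception is made for DLTs.
- *Dose limiting toxicology*: "The DLT assessment period is 12 weeks from the start of treatment". A DLT is an adverse event that meets grade criteria and that the investigator attributes to tolinapant as definite or probable.
- *Dose escalation and determination of MTD*: follow-up without a DLT "is given weight equal to the proportion of the assessment period that has passed". At week 12, "in the absence of a DLT this would account for a full patient tolerable outcome". The same section plans seven weeks of treatment plus five more of DLT follow-up. It counts a patient who stops early for a reason other than a DLT as having had none.
- *Treatment and follow-up visits*: tolinapant is given "prior to radiotherapy on alternate weeks (weeks 1, 3, 5) during chemoradiation", for seven consecutive days each time. After brachytherapy, "Patients will then attend a follow-up visit at weeks 12 and 18, involving physical exams". Both of these visits include an adverse event assessment, and the adverse event row of Table 2 agrees (screening, then weeks 1, 3, 5, 7, 12 and 18).

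**The concern.** The DLT is the primary endpoint, and every DLT is first of all an adverse event. If the rule for reporting adverse events ends before the DLT window does, the article tells sites two different things about the final stretch of that window.

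The error could run in one direction only. A DLT counts as a full event whenever it occurs in the 12 weeks. An unreported one becomes a patient without a DLT, carrying full weight at week 12. Losses of this kind lower the estimated DLT rate at the doses affected and so favour a higher MTD. The recommended phase II dose rests on that estimate.

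**Working it through.** **Inputs.** DLT window: 12 weeks (*Dose limiting toxicology*). Tolinapant: seven days in weeks 1, 3 and 5 (*Treatment and follow-up visits*). Week starts: "Treatment weeks of CRT and tolinapant should always be scheduled to start on a Monday" (Table 2, footnote 1), so week 5 is days 29 to 35. Reporting close: last dose plus 30 days (*Adverse event reporting and risks*). Target DLT rate: 25% (*Dose escalation and determination of MTD*).

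**The plan's own weights.** The article states: "At trial week 6: in the absence of a DLT this would account for 0.5 equivalent of a tolerable outcome". Weight = elapsed days / 84, so week 6 gives 42/84 = 0.5 and week 12 gives 84/84 = 1.0. Treatment plus follow-up is 7 + 5 = 12 weeks. The stated figures reproduce.

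**Gap between the two windows.** Close = last dose day + 30; gap = 84 − close.

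| Last tolinapant dose | Reporting closes | Gap | Share of window | Weight at close |
|---|---|---|---|---|
| Day 35 (full course) | Day 65 | 19 days | 19/84 = 22.6% | 65/84 = 0.774 |
| Day 21 (stops after week 3) | Day 51 | 33 days | 33/84 = 39% | 51/84 = 0.607 |
| Day 7 (stops after week 1) | Day 37 | 47 days | 47/84 = 56% | 37/84 = 0.440 |

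Counting the first dose as day 0 makes the full-course gap 20 days (23.8%). A last dose delayed by 19 days or more would close the gap.

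**What the scheduled visits cover.** Trial week 12 is days 78 to 84. With the one-week tolerance the visit can fall anywhere from day 71 to day 91. A visit on day 71 leaves 84 − 71 = 13 days of the window to be picked up at week 18. No adverse event assessment is scheduled between weeks 7 and 12, while the weight rises from 49/84 = 0.58 to 1.0. Table 2 schedules haematology and biochemistry only up to week 6, although several of the listed DLTs are haematological.

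**Possible effect on the DLT rate.** The documents give no data on DLT timing, so these are assumptions. Apparent rate = true rate × (1 − share of DLTs that fall in the gap and are not captured).

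- All captured at week 12 or 18: 25% stays 25%.
- 10% lost: 25% × 0.90 = 22.5%.
- Even timing, nothing captured after day 65: 25% × 65/84 = 19.3%. Conversely, a true rate of 25% / (65/84) = 32.3% would look like the 25% target.
- 40% lost: 25% × 0.60 = 15%.

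**The case against.** The strongest reply is that the article does provide for collecting DLTs up to day 84. Every patient has an adverse event assessment at week 12 and another at week 18. The design section plans five weeks of DLT follow-up after treatment and, once recruitment stops, has all participants followed to a DLT or 12 weeks. *End of the trial* keeps all patients in follow-up to week 18. On this view the 30-day rule is a general safety reporting rule and does not close DLT ascertainment. For early stoppers, the Safety Review Committee decides whether an extra patient is needed, and patients who withdraw from treatment stay in follow-up where possible. The full protocol, which is not shown, may hold a separate DLT notification rule.

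Much of this stands. A reader might infer that nothing has to be collected after day 65, or that the selected dose will in fact be too high. The documents support neither inference, because the week 12 and 18 assessments are real collection points. Nor do they support a figure for how often too toxic a dose would be chosen: the article leaves the design details to additional file 1, which is not shown, and any simulation would rest on assumed inputs. It would also be a guess to say that 12 weeks was chosen because of late toxicity; the article says only that five weeks are added to seven.

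The reply does not remove the contradiction. Read literally, the reporting rule does not require an event with onset on days 66 to 84 to be reported, even when it is found at a scheduled visit. Sites could reasonably follow either passage. This is not a detail left out of a condensed article: the article states a closing date, and that date conflicts with its own endpoint window.

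**Conclusion.** The contradiction holds and should be corrected. For a full course on schedule, the stated reporting period ends 19 days (23%) before the DLT window; for a patient who stops after the first course it ends 47 days (56%) before. The conflict is with the primary-endpoint window and also with the adverse event assessments at weeks 12 and 18.

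The day counts follow from the article alone. The effect on the estimate does not. Its direction is fixed, since unreported DLTs can only bias the rates downward, but its size depends on how sites resolve the conflict and on when DLTs occur. It is about zero if the week 12 assessment captures all events. It takes a true 25% rate to about 19% if DLTs are evenly spread and nothing after day 65 is captured. That second figure illustrates an unfavourable case and is not a forecast.

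**What to change.** Reconcile the passages in *Adverse event reporting and risks*. Suggested wording: all adverse events and serious adverse events are reported from the first dose of tolinapant until the later of the end of the 12-week DLT assessment period and 30 days after the last dose of tolinapant; this also applies to participants who stop tolinapant early.

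If the full protocol already has a separate rule for reporting DLTs to week 12, refer to it in that section so that sites see one consistent closing date.

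The cost is one sentence and a few more weeks of adverse event entry per patient, using visits already in the schedule. No dose, treatment rule or model setting changes.
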